**Findings::**

By elucidating the healthy food intervention with better health outcomes, this study aims to offer evidence that can guide providers in their recommendations for healthy eating options to patients.

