## Methodology

### Study aims

The primary aim of this study is to compare absolute weight change among participants receiving daily healthy meals or produce box versus matched controls (standard of care) at 16 weeks from baseline:This aim tests the hypothesis that receiving daily healthy meals will result in greater absolute weight loss compared to receiving a produce box or standard of care at 16 weeks from baseline.This aim tests the hypothesis that receiving either daily healthy meals or a produce box will result in greater absolute weight loss compared to standard of care at 16 weeks from baseline.
The secondary aim of this study is exploratory and will compare daily healthy meals or produce box versus matched controls in improving chronic disease markers:This aim tests the hypothesis that receiving daily healthy meals will result in greater improvement in hbA1c and blood pressure compared to receiving a produce box or standard of care box at 16 weeks, six months, and 12 months from baseline.This aim tests the hypothesis that receiving either daily healthy meals or a produce box will result in greater improvement in weight, hbA1c and blood pressure compared to standard of care at 16 weeks, six months, and 12 months from baseline.
To assess whether receiving daily healthy meals or a produce box in conjunction with nutrition counseling and education results in improvement in food insecurity, diet quality, depression, self-efficacy for healthy eating and healthy weight, and self-efficacy for chronic disease management from baseline to 16 weeks.

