### Sample size determination

Similar past research conducted in the US (Berkowitz, Delahanty, *et al.*, 2019) was used to estimate a baseline weight of 92 ± 16 kg for the study population. In order to estimate the effect size of weight loss potential in the intervention groups, the CDC healthy eating standard range of 1 to 2 pounds weight loss per week was used. The estimate for weight loss in the healthy meals group was 2 pounds per week over 15 weeks, and the estimate weight loss for the produce group was 1 pound per week for 15 weeks. It was assumed that there would be no weight change in the matched controls (standard of care) group. A one-way AONVA sample size calculation was performed using the following parameters: mean weight (kg) [matched controls 92, healthy meals 78.4, Produce 85.2], standard deviation 16 for all groups, 0.80 power, and 0.05 alpha. This yielded a sample size of 28 per group. We assume a 10% attrition rate, bringing the sample size to 35 per group.

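### The stated 0.80 power belongs to the three-group omnibus F test, not to the randomised primary hypothesis that meals beat produce

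*Protocol article*

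**What the plan says.** Under Sample size determination, the Protocol article states: "A one-way AONVA sample size calculation was performed using the following parameters". The inputs are "mean weight (kg) [matched controls 92, healthy meals 78.4, Produce 85.2" and "standard deviation 16 for all groups, 0.80 power, and 0.05 alpha". The SD comes from an earlier US study that "was used to estimate a baseline weight of 92 ± 16 kg for the study population". The result is "This yielded a sample size of 28 per group", followed by "We assume a 10% attrition rate, bringing the sample size to 35 per group".

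Under Study aims, the first hypothesis of the primary aim is that "receiving daily healthy meals will result in greater absolute weight loss compared to receiving a produce box or standard of care at 16 weeks". The second is that either food arm beats standard of care. The abstract gives the purpose this way: "By elucidating the healthy food intervention with better health outcomes".

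Under Randomization, only the two food arms are allocated at random, 1:1. Under Study design, the 70 controls are picked from the medical record by matching. Under Data analysis, the outcome is absolute weight change at 16 weeks, analysed by repeated-measures ANOVA with a three-level group factor. Pairwise comparisons are left to post hoc testing. No power is stated for any pair of groups.

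**The concern.** The primary hypotheses are specific contrasts, but the sample size was computed for a test that asks only whether any of three means differs. That test can be significant because meals differ from chart-matched controls, with no evidence that meals differ from produce. The meals-produce question is the one that identifies the better intervention, and it is the only one protected by randomisation.

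At stake is how the result is read. A non-significant meals-produce comparison could be taken as a null from a trial with 80% power, when the 0.80 was never calculated for that comparison. Treating the contrast as a post hoc follow-up to an omnibus F adds to the problem.

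**Working it through.** **Inputs (Sample size determination).** Means: controls 92, meals 78.4, produce 85.2 kg. SD 16 in every group, alpha 0.05. Two-sided testing is assumed, because no sidedness is stated. Arm sizes are 28 (before attrition), 31 (35 × 0.9 = 31.5, rounded down) and 35 (everyone analysed).

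**Step 1: reproduce the plan's figure.** Noncentral F, k = 3, n per group, λ = n × Σ(μᵢ − μ̄)² / SD².
- μ̄ = (92 + 78.4 + 85.2)/3 = 85.2.
- Σ(μᵢ − μ̄)² = 6.8² + (−6.8)² + 0² = 92.48.
- n = 27: λ = 27 × 92.48/256 = 9.75, power 78.9%.
- n = 28: λ = 28 × 92.48/256 = 10.12, df 2 and 81, power 80.5%.

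So 28 is the smallest n reaching 80%, and it is the omnibus test.

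**Step 2: what drives that power.** The produce mean equals the grand mean, so with equal groups produce adds nothing to λ. All of it comes from meals and controls, which lie 13.6 kg apart. As a check, suppose produce worked exactly as well as meals (both 78.4). Then μ̄ = 82.93, λ = 13.49, and omnibus power at 28 per group rises to 90.8%. The omnibus test would be more likely to be significant if the two interventions were identical.

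**Step 3: pairwise power on the same inputs.** Two-sample t test, noncentrality δ = Δ / (SD × √(1/n₁ + 1/n₂)).

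| Contrast | Δ (kg) | n₁ / n₂ | δ | Power |
|---|---|---|---|---|
| Meals vs produce | 6.8 | 28 / 28 | 1.59 | 34.6% |
| Meals vs produce | 6.8 | 31 / 31 | 1.67 | 37.7% |
| Meals vs produce | 6.8 | 35 / 35 | 1.78 | 41.8% |
| Produce vs control | 6.8 | 31 / 63 | 1.94 | 48.3% |
| Produce vs control | 6.8 | 31 / 70 | 1.97 | 49.6% |
| Meals vs control | 13.6 | 28 / 28 | 3.18 | 87.8% |
| Meals vs control | 13.6 | 31 / 63 | 3.87 | 97.0% |

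The 63 controls apply the 10% loss to controls too. The document does not say this, so 70 is shown as well.

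Variants for meals versus produce at 28 per arm: Tukey 21.9%, Bonferroni for three pairs 20.3%, one-sided 0.05 47.0%. The most favourable variant, one-sided with all 35 per arm, gives 54.6%.

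**Step 4: sensitivity to the SD.** SD 16 is the spread of baseline weight, and the document gives no SD of change. The values below are assumptions, for Δ = 6.8 kg and 31 per arm.

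| Assumed change SD (kg) | Power |
|---|---|
| 16 | 37.7% |
| 12 | 59.3% |
| 10 | 75.0% |
| 9.4 | 80.0% |
| 9 | 83.3% |
| 8 | 90.9% |

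If SD is 16 at both visits, then change SD = 16 × √(2(1 − r)). A change SD of 9.4 corresponds to a baseline-to-week-16 correlation of r = 1 − 9.4²/(2 × 256) = 0.83.

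**The case against.** The strongest reply is that SD 16 is the wrong SD for the planned analysis. The outcome is weight change and time is a within-subject factor, so the relevant SD is that of change. If it is about 9.4 kg or less, meals versus produce reaches 80% power at 31 per arm. This stands. A reader might infer from the 35–42% that the trial is in fact badly underpowered for its randomised question. The document does not support that, because without a change SD the real power is unknown.

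It is also fair that the primary aim is framed partly against matched controls, so meals versus produce is one of several contrasts. It is nevertheless named in the first primary hypothesis and stressed in the abstract and the conclusion.

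A reader might also object that the calculation ignores having 70 controls rather than 35. That does no harm: extra controls only raise power (the omnibus figure with 63/31/31 is 94.6%), so assuming equal groups is conservative here.

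Finally, the article claims no pairwise power, lists its small sample as a limitation, and may leave details of the post hoc tests to an analysis plan. That excuses missing detail about the tests. It does not excuse a sample-size target that answers a different question from the primary hypothesis.

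**Conclusion.** The point holds in this form: 0.80 is the omnibus power, and it says nothing about whether meals beat produce. On the plan's own inputs, with two-sided 0.05 and no multiplicity adjustment, that contrast has about 35% power at 28 per arm, 38% at 31 and 42% at 35. Produce versus control has about 48–50% with 31 produce completers and 63–70 controls. Only meals versus control is well powered on these inputs.

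The percentages show that the stated inputs do not support the stated power for the key contrast. They do not predict what the repeated-measures analysis will achieve. The mismatch between the powered test and the hypothesis remains whatever the change SD turns out to be.

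**What to change.** - Prespecify the meals-versus-produce difference in weight change at 16 weeks as a primary contrast that is tested directly, not as a post hoc step after an omnibus F.
- Replace the single 0.80 claim with power or detectable difference for each of meals versus produce, meals versus control and produce versus control. Use the planned sizes (35/35/70), with attrition applied to the randomised arms.
- Base these figures on a stated and justified SD of weight change, and show a range. Repeating the calculation with SD 16 would only carry the unsuitable variance into three more figures.
- Do not enlarge the trial on account of this point.

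The cost is a recalculation and some rewording. The downside is that the stated power for the key contrast may come out less favourable than 0.80.

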### Randomization

Randomization of participants will be conducted using the central randomization module available in the Research Electronic Data Capture (REDCap) program, a secure online database that will be utilized for data collection and management (Harris *et al.*, 2009, 2019). Randomization and allocation will occur in blocks of four. The allocation sequence was generated for a total of 80 participants using randomization software in the Sealed Envelope website (https://www.sealedenvelope.com/simple-randomiser/v1/lists) and uploaded into our study’s REDCap database. Following consent into the study and collection of all baseline data, study participants will be randomly allocated to the healthy meals or produce box group in a 1:1 ratio using the randomization sequence pre-entered into REDCap.

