**Methods::**

This parallel-arm quasi-randomized control trial will be conducted between January 2022 and December 2023. Seventy adult patients recruited from a single academic medical center will be randomly assigned to receive either: i) daily ready-made frozen healthy meals or ii) a weekly produce box and recipes for 15 weeks. Participants will, additionally, take part in one individual nutrition therapy session and watch videos on healthy eating, weight loss, type 2 diabetes, and hypertension. Data on weight, height, glycated hemoglobin, blood pressure, and diabetes and blood pressure medications will be collected in-person at the baseline visit and at 16 weeks from baseline and via medical chart review at six months and 12 months from enrollment. The primary outcome of the study is weight loss at 16 weeks from baseline. Pre- and post-intervention survey data will be analyzed for changes in food insecurity, diet quality, depression, as well as self-efficacy for health eating, healthy weight, and chronic disease management. Through retrospective chart review, patients who received standard of care will be matched to intervention group participants as controls based on body mass index, type 2 diabetes, and/or hypertension.

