### Study design

This study is a parallel-arm quasi-randomized control trial with nonequivalent matched controls, which will be conducted between January 2022 and December 2023. Seventy adult patients recruited from our ambulatory practice will be randomly assigned to receive either: i) daily healthy frozen meals or ii) a weekly produce box and recipes for 15 weeks. Each study arm will comprise 35 patients with a documented diagnosis of obesity (body mass index [BMI] equal to or greater than 30kg/m^2^) and one or more of the following conditions: pre-type 2 diabetes/type 2 diabetes or hypertension. Participants will complete an in-person baseline visit and a follow-up visit at 16 weeks from baseline, and their medical charts will be reviewed for trends in these biomarkers at six months and 12 months from baseline. Healthy meals or a produce box will be shipped to the home address of participants once a week. Healthy meals provided in the study are low-sodium and diabetic-friendly ready-to-heat and serve breakfast, lunch, and dinner items. The produce box provided in the study will comprise fresh vegetables and fruits. For participants receiving a produce box, recipes utilizing items contained in the box will be available at the vendor’s website.

All participants will complete one individual medical nutrition therapy session via phone with a dietitian. The individual medical nutrition therapy appointment will occur within two weeks of enrollment in the study. A total of four nutrition and health videos, each under 10 minutes in length, will be available for participants to view between weeks 3 and 15 of the study. The complete study procedures are outlined in Table 1. Participants will be required to view the videos on healthy eating and weight loss and, as applicable to their health status, videos on type 2 diabetes and hypertension (see Table 2). The Healthie application (https://www.gethealthie.com/?afmc=a46i) will be utilized for nutrition education programming. Through the Healthie application, participants will receive automated text and/or email reminders to view educational videos. This feature is designed to drive compliance and completion of the nutrition education component. A report will be generated to provide completion percentage and other details based on participant engagement. The Healthie application is compliant with the US Health Insurance Portability and Accountability Act.

**Table 1. tbl1:** Schedule of study activities

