### Recruitment strategy

A flyer inviting patients to participate in the study will be available in patient rooms as well as in patient waiting areas at our ambulatory practice. Flyers will have contact information (phone number and email address) for the study coordinator. Potential study participants will be informed about the study by a nurse or provider during their routine office health visits. If interested, potential participants may choose to meet with the study coordinator after their visit or they may call or email the study coordinator at the phone number provided on the tear-off of the study flyer. During phone calls or email correspondence with the study coordinator, eligible participants will receive detailed information about the study, and they will be invited to come to the practice to complete the consent process and baseline visit.

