One limitation of this study is the relatively small sample size of 70 participants who will receive interventions. Consequently, participant attrition from the study will threaten the study power. A second limitation of the study is the lack of a parallel control group. Study controls will consist of 70 matched participants identified via the electronic health record from the same patient population as the intervention arm participants. Due to funding and ethical reasons, this study is unable to utilize a true control group for comparison with the intervention groups. Our study population faces many social challenges, including food insecurity; thus, it is important to ensure that would-be controls receive compensation comparable to the healthy food items received by intervention arm participants. The small amount of the study grant limits the ability to compensate or offer equivalent healthy food items to controls after the intervention period. A third limitation of this study is the relatively short timeline (16 weeks) in which the primary outcome will be assessed. Because this study will offer interventions for only 15 weeks, and to guard against the high attrition common in studies with a lengthy period of follow-up, assessing the primary outcome soon after completion of the interventions is deemed appropriate. With the expected weight loss of one to two pounds a week over the 15-week intervention period, the timeline for the primary outcome is still clinically meaningful. Additionally, biomarkers of interest will be collected via review of the electronic medical record at six months and 12 months from baseline. While these data will allow for the assessment of study outcomes longitudinally, a significant amount of missing data will hinder such a pursuit. A final limitation of the study is the lack of blinding to treatment arm assignment among assessors collecting self-reported data. To mitigate this limitation, during the baseline visit, self-reported data will be collected prior to random allocation to intervention arms. In addition, the biostatistician analyzing the data will be blinded to the treatment arms. Despite the aforementioned limitations, we anticipate that the results of this study will add to the growing body of scholarship on the impact of direct healthy food interventions on chronic diseases.

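### With one fixed block size of four, recruiting staff who know it and keep a tally could work out about a third of the meals or produce box allocations in advance

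*Protocol article*

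**What the plan says.** The Randomization section of the protocol article sets the block size: "Randomization and allocation will occur in blocks of four". The list already exists: "The allocation sequence was generated for a total of 80 participants". Once consent and the baseline measurements are complete, "study participants will be randomly allocated to the healthy meals or produce box group in a 1:1 ratio using the randomization sequence pre-entered into REDCap". No stratification is described, and no second block size.

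The abstract's Methods and the Study design section place the trial at one site: "Seventy adult patients recruited from a single academic medical center" and "Seventy adult patients recruited from our ambulatory practice will be randomly assigned to receive either" one of two foods, which are shipped weekly to the home. The control group is drawn afterwards from the medical record and is not randomised.

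Under Recruitment strategy, patients respond to a flyer or hear of the study from a nurse or provider. Then "potential participants may choose to meet with the study coordinator after their visit", or they call or email. Those who are eligible receive details and "they will be invited to come to the practice to complete the consent process and baseline visit".

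On blinding, Strengths and limitations says: "A final limitation of the study is the lack of blinding to treatment arm assignment among assessors collecting self-reported data". The biostatistician is blinded.

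**The concern.** With a constant block of four at 1:1, each arm has exactly two places in every block. Once both places of one arm are used, the rest of the block is known. With one centre and one list, past allocations form a single short sequence, and a frozen-meal delivery cannot be mistaken for a produce box. A person who knows the block size and keeps a tally can therefore sometimes name the next allocation before a patient is booked.

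Hiding the list in REDCap does not help, because the deduction uses past assignments and not the list. Randomising after consent and baseline protects the baseline measurements and prevents a change of mind after consent. It does not cover whom to invite and when, which is decided earlier.

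Meals versus produce box is the only contrast that randomisation protects. It is part of the first primary hypothesis in Study aims and the comparison that the article presents as new. With 35 per arm, steering even a few patients (for example, those thought readier to cook, or more motivated) could make the arms differ at entry. The contrasts with matched controls are not randomised, so concealment protects nothing there.

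**Working it through.** The article gives no figure for predictability, so there is none to reproduce.

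**Inputs.** Block size 4, ratio 1:1 and list length 80 (Randomization); 70 participants to be randomised (Study design); one centre (abstract, Methods). The list is 80/4 = 20 complete blocks. The planned sample is 70 = 17 × 4 + 2, that is, 17 complete blocks plus two participants.

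**Assumption.** The recruiter knows the block size and the order of past allocations. The article states neither this nor the opposite.

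**Step 1: allocations known with certainty.** There are six equally likely blocks, with A and B for the two arms.

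| Blocks | Positions determined | Count per block |
|---|---|---|
| AABB, BBAA | 3rd and 4th | 2 |
| ABAB, ABBA, BAAB, BABA | 4th only | 1 |

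- Mean per block: (2 × 2 + 4 × 1)/6 = 8/6 = 1.33, and 1.33/4 = 33.3%.
- Over 70 participants: 17 × 8/6 = 22.7, which is 32.4%. The two participants in the incomplete block are never determined.
- Over the full list of 80: 20 × 8/6 = 26.7, which is 33.3%.

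**Step 2: best guess.** The strategy is to name the arm that is behind, and to toss a coin when the arms are level.

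- Chance of being right by position: 1/2, 2/3, 2/3, 1. At the third position this is 1/3 × 1 + 2/3 × 1/2 = 2/3.
- Sum: 2.83 of 4, or 70.8%. Over 70: (17 × 2.83 + 1.17)/70 = 49.3/70 = 70.5%.
- This strategy needs no knowledge of the block size, because the tally returns to level at the end of every block.

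**Step 3: alternatives.** The random mixes were simulated on 300 lists of 70. The recruiter was assumed to know the set of sizes but not their order.

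| List | Known with certainty | Best guess right |
|---|---|---|
| Fixed 4 | 33.3% | 70.8% |
| Fixed 6, size known | 1.5/6 = 25% | 4.10/6 = 68.3% |
| Fixed 8, size known | 1.6/8 = 20% | 66.6% |
| Random 4 and 6 | 5.5% | 69.1% |
| Random 4, 6 and 8 | 2.0% | 68.1% |

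For the 4 and 6 mix, direct arithmetic on the best guess agrees: (2.83 + 4.10)/10 = 69.3%. In participants, certain predictions fall from about 23 to about 0.055 × 70 = 3.9, or four. A larger fixed block removes much less certainty than a varying one.

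**Step 4: cost in balance.** The largest imbalance when recruitment stops inside a block is half the block size: 2 for blocks of four, 3 for blocks of six.

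**The case against.** The strongest reply is that the article describes sound practice: a pre-loaded list, central allocation, and randomisation only after consent and all baseline data. Nothing in it is contradictory. Prediction needs someone who knows the block size and tracks the order, and no section says that the coordinator, nurses or providers do. Who may see the list is detail that a condensed article commonly leaves to the full protocol, so silence on it is no finding. This stands, and it makes the one-third figure conditional. It does not remove the point, because the constant block size is stated and is a choice.

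The steering route is also conjectural. Patients come forward themselves or through a clinician, eligible ones are invited, and no text gives the coordinator discretion over whom to invite. Both arms receive free food and counselling, so there is no untreated arm to avoid. This lowers the likelihood. But the foods ask different things of the patient, and the timing of visits is open.

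Four stronger readings are tempting, and the documents do not support them:

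- That staff will foresee a third of allocations. This holds only under the assumption above.
- That the fix restores full unpredictability, from 71% to 50% correct guesses. The 50% belongs to simple randomisation; varying blocks of 4 and 6 still leave about 69%.
- That any resulting imbalance is beyond adjustment. Weight, HbA1c, blood pressure, medications, food insecurity, diet quality, depression and self-efficacy are all recorded at baseline, so imbalance in these would be visible and partly adjustable. Motivation and readiness to cook are not directly measured.
- That all outcome assessors are unblinded. The stated limitation concerns self-reported data, whereas the primary outcome is measured weight, and no section says that these assessors recruit.

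**Conclusion.** The point holds as a conditional weakness. If recruiting staff know or infer the block size and track allocations, about 33% of assignments (about 23 of 70) are determined in advance, and the stated safeguards act too late to prevent it. The enumeration is exact. What remains uncertain is whether anyone would have the knowledge and use it.

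This is a potential weakening of concealment in the only randomised comparison, not a failure of concealment and not evidence of bias. Adjustment could deal with part of an imbalance in measured baseline variables, but not with unmeasured traits such as motivation. Importance is moderate, and the remedy is cheap. What it buys is the removal of most certain predictions; overall guessing success hardly changes.

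**What to change.** Generate the allocation list with randomly varying block sizes, for example a random mix of 4 and 6, and do not disclose the sizes to staff who recruit, consent or book patients. Because the list of 80 already exists, replace its unused part in the same way, preferably from the end of a completed block so that the change itself adds no imbalance. Simply moving to a larger fixed block would not do: a known block of 6 still determines 25% of allocations.

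If enrolment is complete, the sponsor can still report who knew the block size, and compare baseline characteristics between participants at determined and undetermined list positions.

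The cost is one regenerated list and one upload to REDCap. The downside is a possible final imbalance of up to three participants between arms, against up to two with blocks of four.
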